# The effects of repetitive transcranial magnetic stimulation in obese females with binge eating disorder: a protocol for a double-blinded, randomized, sham-controlled trial

**DOI:** 10.1186/s12888-015-0569-8

**Published:** 2015-08-12

**Keywords:** Binge eating disorder, Transcranial magnetic stimulation, Neuroimaging, Hormones, Eating disorders, Obesity, Control inhibition, Eating disorders

## Abstract

**Background:**

Binge eating disorder is a new category in DSM-5 and highly associated with higher body mass index. The neural mechanisms that underlie binge eating are of great interest in order to improve treatment interventions. Brain mechanisms underlying drug and food craving are suggested to be similar: for example, both are reported to be associated with increased neural activity in the orbitofrontal and anterior cingulate cortex, and a diminished regulatory influence from lateral prefrontal circuits. Several studies have begun to assess the potential benefits of brain stimulation in reducing craving and addictive behaviors. Data from a study of a one-off session of transcranial magnetic stimulation in healthy women identified as strong cravers and of individuals with bulimic-type eating disorders, reported a reduction in food craving and binge eating episodes. This provides support for a more extensive investigation of the potential therapeutic benefits of transcranial magnetic stimulation. Lastly, brain imaging studies and a dimensional approach, will improve understanding of the neural correlates of the disorders and of the mode of action of transcranial magnetic stimulation.

**Methods/Design:**

Sixty eligible obese females, with binge eating disorder, will be randomly allocated to receive 20 sessions of transcranial magnetic stimulation intervention (*n* = 30) or the sham transcranial magnetic stimulation intervention (*n* = 30) scattered 3 days/week. Thirty eligible controls will complete the baseline assessment. The primary outcome (number of binge eating episodes) will be assed at each treatment sessions, and 8 weeks after intervention completion (follow-up). It is hypothesized that mean weekly binge-eating episodes will be reduced in the intervention group, compared to the sham group, and that the effect will be maintained at follow-up.

**Discussion:**

Despite the severity associated with Binge Eating Disorder, there are limited treatment options. This study is an important step in the development of more effective treatments. Importantly, the study is the first to investigating binge eating disorder using a dimensional approach, by looking at the different aspects of the disorder, such as behavioral factors, biological factors, brain circuits and chemistry.

**Trial registration:**

Clinical Trials NCT02180984. Registered in July 2014.

**Electronic supplementary material:**

The online version of this article (doi:10.1186/s12888-015-0569-8) contains supplementary material, which is available to authorized users.

## Background

### Introduction

Binge Eating Disorder (BED) is characterized by recurrent episodes of excessive food consumption with experienced loss of control over eating and marked distress, which are not regularly followed by inappropriate compensatory behaviors [1]. Originally, BED was introduced in the 4th edition of the Diagnostic and Statistical Manual of Mental Disorder (DSM-IV) as a subcategory of Eating Disorder not Otherwise Specified (EDNOS) [2], but is now a separate diagnostic entity. The DSM-5 diagnostic criterion for BED includes significant changes. The minimum average frequency of binge eating (BE) has been reduced from at least twice/week for six months to at least once/week for three months.

BED is a clinically significant disorder affecting a broader range of individuals than anorexia nervosa (AN) and bulimia nervosa (BN) [3]. The lifetime prevalence of BED is higher in overweight and obese population [4], with numbers as high as 51 % of individuals seeking help in weight loss programs in Latin America [5]. In addition, BED is a long-term disorder, with a mean lifetime duration of 14.4 years [6] and, lastly, it is associated with significant impairment in quality of life, i.e. (both physical and mental health) [4, 7].

Despite the emotional and physiological consequences of BED, effective treatment associated with a long-term impact on weight is limited. Cognitive Behavioral Therapy (CBT) is currently the treatment of choice: it is reported to result in a 60 % long-term (one year) reduction in BE [8, 9]. However, with respect to weight loss, the impact of psychological interventions for BED is limited [10]. Similarly, despite reducing the frequency of BE, drug treatments are associated with little effect on weight, (with few exceptions such as sibutramine and topiramate [10–12]). Unfortunately, these medications are associated with safety restrictions: sibutramine has been withdrawn from the market in many countries, and topiramate has been associated with low tolerability [13]. Importantly, the paucity of information on the pathophysiological mechanisms underlying BED, is limiting further advances in treatment.

It is clear that, there is a need for a broader investigation of the mechanisms that are involved in the genesis and maintenance of BED, e.g. of the neurobiological processes underpinning bulimic behaviors and weight regulation. This type of exploration is in accordance with the US National Institute of Mental Health (NIMH) and the Research Domain Criteria (RDoC), which is a new research approach scientists are being encouraged to adopt it. In essence, the RDoC is a dimensional research approach that investigates mental disorders by looking at different aspects, such as behavioral factors, biological factors, brain circuits and chemistry [14]. The current project was based on the RDoC approach and guidelines; hence, different units of analysis and aspects of BED will be investigated.

### Psychoneuroendocrinological and immunological aspects of BED and obesity: food craving, stress, hormones and their association with control inhibition and compulsive eating

There is increasing interest in the conceptualization of disordered eating as a food addiction. This is substantially based on the fact that that addictions and bulimic type ED share phenomenological characteristics such as escalating frequency of the behavior, increased salience of food/drug stimuli, ambivalence towards treatment and frequent relapse [15, 16]. In terms of brain mechanisms, individuals who are drug addicts and obese (with and without BED), are reported to have decreased DA D2 receptor density in the striatal regions [17–19]: this may reduce the sensitivity to natural rewards and enhance impulsivity [20]. It has been hypothesized that impulsivity results from failures of response inhibition or ‘top down’ cognitive control involved in the activity of the prefrontal cortex (PFC), specifically the dorsolateral prefrontal cortex (DLPFC). Individuals with effective dietary self-control have increased activity in the left DLPFC when making decisions about food ingestions [21], suggesting that the DLPFC may be important for regulatory control over food consumption.

Abnormalities in the food reward system and BE may be associated with emotional and physiological stress. Cortisol, the primary effector of the hypothalamic-pituitary-adrenal (HPA) axis, may mediate stress-induced eating and play a role in disordered eating [22]. Stress is not only associated with disruption of the HPA axis, but may also sensitize pro-inflammatory responses known to take part in the pathogenesis of several ill-health conditions, including psychiatric disorders and obesity. For instance, the adipose tissue is part of the endocrine and innate immune systems [23]. During the fat storage process, adipose tissue produces inflammatory cytokines, such as C-reactive protein, TNF-alpha and IL-6. Importantly, adiponectin synthesis is reduced in obese individuals [24], and the mechanism that trigger the peripheral inflammation has a cascade effect in the hypothalamus [25], leading to the dysregulation in the physiological responses that maintains the sensitivity to insulin, leptin, ghrelin and peptide tyrosine tyrosine (PYY). Furthermore, stress and inflammation have been implicated in the disruption of synaptic signaling and integrity, a process mediated in part through the inhibition of neurotrophins’ function, in which BDNF is the most extensively characterized [26]. Beyond its importance in neural development and synaptic plasticity, there is evidence [27] indicating that BDNF is also essential for weight control and is involved in both homeostatic and non-homeostatic eating. In animal models [28], BDNF has anorexigenic effects in the hypothalamus.

Ovarian hormones are also involved in regulating food intake. Exacerbation of BE seems to occur when estrogen levels are low (premenstrual phase), and when progesterone levels are high (mid-luteal phase) [29]. Estrogen is mostly produced in the ovaries, but also in the liver, adrenal glands and fat tissue. Together with progesterone, ghrelin, leptin, PYY and BDNF, estrogen has a role in appetite regulation [30]. It is known that hormonal dysregulation, including estrogen, has an impact on mood, body weight and shape satisfaction, and on anxiety symptoms [31]. Further, estrogen has both anti-inflammatory and pro-inflammatory roles in the nervous system [32].

### Cognition & neuropsychological evaluation of BED

Neuropsychological research involving individuals with BED has demonstrated that in this group, cognitive performances are poorer on some executive functional tasks, such as, set shifting, inhibitory control [33], planning, decision making [34, 35], problem solving, attention, and working memory [36] than in healthy controls. However, the exactly cognitive profile and mechanism abnormalities of individuals with BED have not been established yet. Notably, the literature suggests that a similar cognitive impairment profile is present in obese individuals with or without BED, indicating that cognitive deficits may be related to obesity itself rather than to the ED [33, 34, 37], pointing out the need for further research.

Moreover, the use of neuropsychological instruments along with neuroimaging is important to identify mild cognitive impairments and create the opportunity to distinguish brain patterns associated with a specific disorder. A recent study [38] that used fMRI to investigate the neural correlates of inhibitory control in obese participants with BED (*n* = 35) found hypoactivity in brain regions involved in self-regulation and impulse control in obese BED participants during a cognitive control task (Stroop test) compared with obese non-BED and lean controls. The obese group with BED showed diminished activity in the ventromedial prefrontal cortex (vmPFC), inferior frontal gyrus (IFG) and insula. The authors concluded that the abnormalities in the activation of brain areas related to inhibition control in obese people with BED support the hypothesis that obese binge eaters differ from other obese individuals in regards to neurobiological aspects, including inhibitory control abilities. The study was the first to investigate the neural correlates of control inhibition in obese individuals with BED in comparison to lean controls.

The CPT-IP is a tool used to evaluate behavior inhibition and cognitive impulsivity [39]. A recent and small fMRI study with healthy subjects, using CPT to investigate brain regions involved during the CPT performance: it identified the left cerebellum and the frontal, temporal and occipital cortical brain areas. The ACC was identified with the greatest activation cluster during the same task [40]. Studies report that rTMS may lead to a better cognitive performance [41, 42], however further studies are necessary to understand its mechanisms of actions.

### Repetitive Transcranial Magnetic Stimulation (rTMS) for the treatment of BED

It has not been established whether the clinical benefit of any of the rTMS protocols in psychiatric disorders are a direct or indirect consequence of the modulation of neuronal excitability. It has been proposed that the associated release of neuromodulators and growth factors, e.g., brain derived neurotrophic factor (BDNF) [43], play a role in the mechanisms of action of rTMS [44].

There are pilot research studies on the effects of TMS on food cravings and bulimic behaviors in humans. A groundbreaking research study [45], demonstrated that rTMS applied to the left PFC might inhibit food craving compared to sham rTMS in healthy women considered “strong cravers.” An earlier small (*n* = 14) and unpowered, randomized, sham controlled trial found no benefit for the use of rTMS to control bingeing or purging behaviors in bulimic subjects [46]. In contrast, a subsequent proof-of-concept trial [47] reported positive findings of a one-off session of real rTMS compared to sham treatment for the reduction of food craving and BE in the 24 h follow-up in individuals with bulimic-type disorders. Furthermore, two recent reports have demonstrated rTMS to be an effective treatment for refractory bulimic-type ED. The first case report described a female with a diagnosis of both refractory BN and comorbid depression [48], and demonstrated that 20 sessions of rTMS (five sessions per week over four weeks) ameliorated depression symptoms, BE behaviors and purging, during the treatment. The second and most recent case report [49], described a young female diagnosed with refractory BED and comorbid depression. She was treated with 20 sessions of rTMS to the left DLPFC for 30 min/session at 10Hz for one month [2400 stimuli per day]),: this resulted in partial, but significant remission of depression symptoms and BE. Durability of clinical benefit of rTMS treatment has not been established, but studies that examined the short-term durability of rTMS effects on depressive symptomology demonstrated positive results [50, 51]. Repetitive TMS also holds promise as a tool for managing brain network plasticity properties and modulating cognitive abilities [52], and there is evidence that the intervention might be associated with up regulation of BDNF and possible neuroprotective effects [53].

Studies have also addressed the impact of rTMS on HPA axis function in humans [54, 55]. To date, the most consistent results are found for individuals with depression disorder. In this population, rTMS seems to reduce HPA axis activity. The effects of rTMS on the stress response in patients with bulimic-type ED have also been investigated in a double-blinded randomized sham-controlled trial study [47]: twenty-two female participants received a one-off session of high-frequency rTMS delivered to the left DLPFC, and salivary cortisol levels were assessed at four time points throughout the 90-min trial. Results showed that salivary cortisol concentrations of individuals receiving real rTMS were significantly lower compared to the individuals receiving sham rTMS.

Based on previous findings, rTMS is an important research tool to investigate the neurobiology of craving and BE. Thus, the current randomized controlled trial was developed to investigate the effects of rTMS on food craving and BE behavior, but secondary aims include the study of its effects on ED-related psychopathology (including depression, anxiety and stress symptoms), anthropometric measures, cognition, brain structure and function, hormones and inflammatory biomarkers. In addition, tolerability and safety of rTMS will be examined.

The study will provide the opportunity to enhance the knowledge on etiological similarities between addictions and bulimic disorders. It will also enable the investigation of the interplay of neurobiological mechanisms that are potentially involved in the pathogenesis of BED, and which might be vulnerable to the effects of rTMS.

### Hypothesis

Primary hypothesis:

The rTMS intervention will lead to the reduction of BE frequency and food craving.

The secondary hypothesesrTMS will promote a reduction in ED psychopathology (BES, TEF-Q, LOCES, BSQ,) and associated psychopathology (DASS-21, UPPS), a reduction of anthropometric measures (BMI, hip-waist circumference ratio) and an improvement in neurocognitive performance (Stroop test, executive functioning battery, particularly the CPT-IP).Following rTMS, plasma leptin and estrogen will be decreased along with cortisol levels and proinflammatory biomarkers (PCR, TNF-alpha, IL-6, IL-10) and that there will be an increase in plasma levels of ghrelin (in participants with >20 % of weight reduction), in levels of PYY and BNDF, as well as other anti-inflammatory biomarkers (adiponectin and IL-2).Participants will show that better inhibitory responses and greater activation in response inhibition regions (e.g. the DLPFC).There will be no differences between groups in prevalence of adverse events and dropout rates.Effects will be maintained at 8-weeks follow-up.

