#### Primary outcome measures

The primary outcomes of this study are: (1) the change in the number of BE episodes before and after study treatment (number of BE episodes at baseline subtracted from the number of BE episodes at the end of treatment), as measured by participants recording of binge episodes in the food diary during the previous 15 days to the baseline visit (first rTMS session, T.3) to the end of treatment visit (T.23); (2) the change in “urge to eat” (craving) as measured in a 10 cm VAS (from T3 to T22).

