### Sample size and statistical analysis

To detect the change in craving and BE frequency before and after treatment intervention, the following parameters were used to estimate sample size: effect size *f* = 0.31 (supposed to be small), alpha error probability =0.05, power = (1-β error probability) = 0.8, number of groups = 2, number of measurements through the follow-up = 3 and correlation among repeated measurements = 0.5.

Statistical Inferences: Two different types of analyses will be used to evaluate the effectiveness of the rTMS. The first (and standard) method is intention-to-treat (ITT) that assumes that every patient allocated to be intervention actually received it [75]. The other paradigm, CACE estimation method [76, 77] will take into account the compliance status (patient’s adherence to the rTMS).The compliance status is defined here as at least one of 20 session of rTMS; CACE estimation, therefore, provides a realistic effect under non-adherence phenomenon being estimated based on the structural equation modeling. Underlying both paradigms, it will be used growth modeling, which examines the development of individuals on one more outcome variables over the time. In growth modeling (on contrary of repeated ANOVAS), random effects are used to capture individual differences in development. The corrected significance level (Bonferroni) to be adopted due to 32 outcomes will be 0,0015. Such procedure will be carried to avoid false discovered rate due to multiple comparisons. All the statistical inference will be done via Mplus 7.0. In addition, careful fMRI image acquisition and processing will be completed and analyzed taking into consideration the limitations of fMRI studies.

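### Two primary outcomes are named in the body and one in the abstract, with no rule for success; the stated 80% power covers one outcome at a time

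*Protocol article*

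**What the plan says.** The Hypothesis section of the protocol article gives a single primary hypothesis covering two effects: "The rTMS intervention will lead to the reduction of BE frequency and food craving". The section on primary outcome measures makes both primary. It begins "The primary outcomes of this study are: (1) the change in the number of BE episodes before and after study treatment" and then adds the change in urge to eat on a 10 cm visual analogue scale. The abstract names one only: "The primary outcome (number of binge eating episodes) will be assed at each treatment sessions".

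The section on sample size and statistical analysis names both outcomes as the target of the sizing: "To detect the change in craving and BE frequency before and after treatment intervention, the following parameters were used to estimate sample size". It then gives one set of inputs: a single effect size f of 0.31, "alpha error probability =0.05", "power = (1-β error probability) = 0.8", two groups, three measurements, and a correlation of 0.5 among the repeated measurements. That correlation runs across time within one outcome, not between the two outcomes. The same section sets a Bonferroni level of 0.0015 per outcome over 32 outcomes.

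No section says whether the primary hypothesis is confirmed by both outcomes, by either one, or by BE episodes alone.

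**The concern.** The power figure is attached to a sentence naming two outcomes, but its inputs can describe only one. There is no second effect size, no correlation between outcomes and no joint success criterion. A reader cannot tell what the 80% is the probability of.

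The result is also left open. If BE episodes reaches significance and craving does not, the abstract suggests a positive trial. The primary hypothesis can be read as unconfirmed, and the list of primary outcomes gives no answer. The reverse split is just as unclear. Without a fixed rule, the reading could be chosen after the results are known. The gap is separate from the choice of 0.0015, because it exists at the sizing's own alpha of 0.05.

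**Working it through.** **Inputs from the documents.** f = 0.31, alpha 0.05, target power 0.8, g = 2 groups, m = 3 measurements, rho = 0.5 over time (Sample size and statistical analysis); N = 60, 1:1 (Overview and study design; Randomization); 0.0015 per outcome, close to 0.05/32 = 0.00156.

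**Assumptions, not in the documents.** f = 0.31 holds for both outcomes. The two test statistics correlate r = 0 to 0.7.

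**Step 1: reproduce the sample size.** For the between-group test in a repeated-measures ANOVA, the noncentrality is lambda = f² × N × m / (1 + (m − 1) × rho), on 1 and N − 2 degrees of freedom.

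- At N = 60: lambda = 0.0961 × 60 × 3 / 2 = 8.65 on 1 and 58 df, giving power of 82.4% at alpha 0.05.
- The smallest even N reaching 80% is 58 (81.1%), two short of 60.
- If f is applied to the time effect or the group-by-time interaction, N = 20 is enough, so those versions do not lead to 60.

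The 60 therefore fits a single-outcome calculation on the between-group test.

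**Step 2: power under each reading.** Let p be the power per outcome. Power for both is the bivariate normal probability at z = Φ⁻¹(p) in each coordinate, with correlation r. Power for at least one is 2p minus power for both. At r = 0 and alpha 0.05, power for both is 0.8243² = 0.679, and for at least one it is 2 × 0.8243 − 0.6795 = 0.969.

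| What counts as success | Each test at 0.05 | Each test at 0.0015 |
|---|---|---|
| BE episodes alone | 82.4% | 35.9% |
| Both outcomes, r = 0 to 0.7 | 67.9% to 74.4% | 12.9% to 24.1% |
| At least one, r = 0 to 0.7 | 96.9% to 90.4% | 58.9% to 47.7% |

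At alpha 0.05, the values for both are 67.9%, 70.2%, 72.1% and 74.4% for r = 0, 0.3, 0.5 and 0.7. Starting from a nominal 80% per outcome instead of 82.4%, they are 64.0%, 66.6%, 68.7% and 71.3%.

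**Step 3: error rate if either outcome suffices.** Two independent tests at 0.05 give 1 − 0.95² = 9.75% false-positive risk. Splitting alpha to 0.025 each controls this. Power per outcome is then 73.7%, and the chance of at least one win is 93.1% (r = 0) to 84.0% (r = 0.7).

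**Step 4: size needed for 80% on both at alpha 0.05.** Total N is about 74, 72 or 70 for r = 0, 0.3 or 0.5.

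**The case against.** A reader might infer that the primary hypothesis requires an effect on both outcomes, so that the trial's real power is 68 to 74% instead of 80%. The documents do not support that as a flat statement:

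- No section states an all-must-win rule. The secondary hypotheses list many expected effects in the same style, and nobody would read those as needing simultaneous success.
- A Bonferroni correction over 32 outcomes treats each outcome as its own claim. A both-must-win rule would need no such correction.
- The abstract names BE episodes alone. On that reading power at alpha 0.05 is 82.4% and there is no shortfall. If either outcome suffices with alpha split, the chance of at least one win is also above 80%.
- The 68 to 74% is calculated at 0.05, which is not the level the analysis plans to use.
- The between-group test is inferred because it comes close to N = 60. It compares averages over three measurements, whereas the primaries are defined as changes. If f = 0.31 were meant for the group-by-time interaction, power at N = 60 would exceed 99.9% per outcome, although that version does not produce 60.

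All of this stands, and it makes the joint figure conditional. One further argument, that a success rule is commonly left to the analysis plan and that quoting power per outcome is normal practice, carries less weight. The article itself gives different primary outcomes in the abstract and the body, and it attaches one outcome's power to a sentence about two. Those are faults in the printed text.

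**Conclusion.** The point holds in a conditional form. The protocol article names two primary outcomes in the Hypothesis, primary outcome and sample-size sections but one in the abstract, and gives no success rule. Its 0.8 is power per outcome: 82.4% at N = 60 and alpha 0.05 on the test that best reproduces the sample size.

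A shortfall at alpha 0.05 arises if both outcomes are required: joint power is then about 6 to 12 points below the printed 80%. At the planned 0.0015, no reading reaches 80% on this test. The figures rest on f = 0.31 being true for both outcomes, an assumed correlation of 0 to 0.7, and the between-group test. They do not show that the trial was meant to succeed only on both.

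The firm conclusion is that the primary claim and its power need to be tied to one stated rule. This should be settled before results are seen.

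**What to change.** In the section on sample size and statistical analysis, state that 0.8 is power per outcome. Then take the two primaries out of the 32-outcome Bonferroni set and test them in fixed sequence: BE episodes first at 0.05, and craving at 0.05 only if BE episodes is significant. Keep the Bonferroni correction for the secondary outcomes, with the divisor recounted if the 32 included the primaries. Bring the abstract, the Hypothesis section and the section on primary outcome measures into line with this order.

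This holds the error rate over the two primaries at 0.05, matches the alpha used in the sizing, and gives BE episodes 82.4% power instead of 35.9%. It also respects the abstract, where BE episodes is the only primary outcome.

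The cost is a few sentences and no extra patients. There are three downsides:

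- Craving cannot be claimed if BE episodes fails.
- The multiplicity rule must be reworded, and the 0.05 error control then applies to the primary and secondary families separately, not to all 32 outcomes together.
- The chance of claiming both outcomes stays at about 68 to 74% under the assumptions above. If the sponsor does want both to be required, that figure should be printed, or the sample size raised to roughly 70 to 74.

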##### Biomarkers

Blood serum levels of reactive-C protein, BDNF, adiponectin, TNF-Alpha, IL-6, IL-10, leptin, ghrelin, PYY_3–36_, estradiol and progesterone will be measured in order to analyze changes in inflammatory response, hormones and neurotrophic factors.

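### The ghrelin hypothesis is conditioned on weight loss after randomisation, and IL-2 is hypothesised but missing from the blood-marker list

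*Protocol article*

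**What the plan says.** The second of the secondary hypotheses (Protocol article, Hypothesis) lists how blood markers should move after rTMS. For ghrelin it says that "there will be an increase in plasma levels of ghrelin (in participants with" a weight loss above 20 %). It then names PYY and BDNF, "as well as other anti-inflammatory biomarkers (adiponectin and IL-2"), as further markers expected to rise. The hypothesis before it expects BMI to fall with rTMS.

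The Biomarkers section gives the blood markers to be measured. It opens with "Blood serum levels of reactive-C protein, BDNF, adiponectin, TNF-Alpha, IL-6, IL-10, leptin, ghrelin", continues with PYY, and closes with "estradiol and progesterone will be measured in order to analyze changes in inflammatory response, hormones and neurotrophic factors". Ghrelin is on this list without any weight-loss condition. IL-2 is not on it.

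The section on sample size and statistical analysis names intention-to-treat as the standard method, with CACE estimation and growth modelling beside it. It sets a Bonferroni level of 0.0015 for 32 outcomes, which it does not list. It defines no subgroup by weight loss.

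**The concern.** Two separate defects sit in one sentence of the hypotheses.

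- **Ghrelin.** Losing more than 20 % of body weight is an outcome, and the protocol itself expects treatment to affect weight. If rTMS changes who reaches the threshold, the rTMS women and the sham women in the subgroup are selected differently, and a difference in ghrelin between them cannot be credited to rTMS. Reading the hypothesis as a before-after change within the rTMS arm does not help: that gives up the sham control and keeps the selection. The threshold is also demanding for a trial of this length, so the comparison may have almost no one in it.
- **IL-2.** One section promises a result for a marker that the section on blood measurements does not include.

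At stake are a ghrelin answer that is biased or uninformative although ghrelin is measured, and an IL-2 prediction with no visible source of data.

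**Working it through.** **The plan's own figures.** The protocol gives no expected weight loss and no size for the ghrelin subgroup, so there is no figure to reproduce on this point. The Bonferroni level does reproduce: 0.05 / 32 = 0.00156, stated as 0.0015.

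**How demanding the threshold is.** From the protocol: BMI of at least 35 and weight of at most 150 kg (inclusion criteria), about 7 weeks of treatment (Participants), follow-up 8 weeks later (Overview and study design), hence 7 + 8 = 15 weeks. Height is not given; 1.50 to 1.70 m is my assumption. Weight = 35 × height²; loss = 0.20 × weight.

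| Case | Weight (kg) | 20 % loss (kg) | kg/week over 7 | kg/week over 15 |
|---|---|---|---|---|
| BMI 35, 1.50 m | 78.75 | 15.75 | 2.25 | 1.05 |
| BMI 35, 1.60 m | 89.6 | 17.92 | 2.56 | 1.19 |
| BMI 35, 1.70 m | 101.15 | 20.23 | 2.89 | 1.35 |
| Weight limit | 150 | 30 | 4.29 | 2.00 |

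**How many women might qualify.** Two sets of assumptions, both mine.

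(a) Percentage weight change is normal with mean μ and SD σ, and the expected count is 60 × Φ((−20 − μ)/σ). Means from 0 to −5 % with SD 3 to 7 % give 0 to 1.0 women. A mean of −8 % with SD 7 % gives 60 × 0.0432 = 2.6.

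(b) A fixed rate p, the same in both arms of 30. The expected count is 60p, and the chance of at least one woman in each arm is (1 − (1 − p)^30)².

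| p | Expected of 60 | At least 1 in each arm | At least 2 in each arm |
|---|---|---|---|
| 1 % | 0.6 | 6.8 % | 0.1 % |
| 2 % | 1.2 | 20.7 % | 1.5 % |
| 5 % | 3 | 61.7 % | 19.9 % |
| 10 % | 6 | 91.7 % | 66.6 % |

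**What such a subgroup could detect.** Standardised difference d with 80 % power, two-sample t-test, two-sided:

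| Women per arm | α = 0.05 | α = 0.0015 |
|---|---|---|
| 3 | 3.1 | 7.9 |
| 5 | 2.0 | 3.7 |
| 30 (all randomised) | 0.74 | 1.08 |

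Even the 10 % rate, about 3 women per arm, leaves only enormous differences detectable.

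**Hypothesised against measured markers.** The hypothesis names 12: leptin, estrogen, cortisol, C-reactive protein, TNF-alpha, IL-6, IL-10, ghrelin, PYY, BDNF, adiponectin and IL-2. Ten appear in the Biomarkers section (estrogen as estradiol), beside progesterone, which has no stated direction. Cortisol is not there but is covered by the salivary samples described with the Food Challenge Task under Neuroimaging. IL-2 alone has no measurement in any section shown.

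**The case against.** The strongest reply is that the 20 % condition is a scientific expectation and not an analysis rule. The Biomarkers section puts no weight-loss limit on ghrelin, and the statistics section plans intention-to-treat and defines no such subgroup, so the default analysis may already be the right one. This stands in part. A reader might infer that the ghrelin hypothesis cannot be tested at all; the documents do not support that, since ghrelin is measured and the comparison could be computed if enough women passed the threshold. The hypothesis as worded is still conditional on weight loss, and an unconditional analysis would answer a different question.

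A reader might also infer that the subgroup will be practically empty. The protocol does not establish this. Its remark that "drug treatments are associated with little effect on weight" concerns drugs, and allows for exceptions; its companion remark concerns psychological treatment. Neither is about rTMS. They are indirect support, as is the rule that a woman who starts an excluded weight-reducing medication is withdrawn. Very small is a fair inference; near zero is not a finding.

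On IL-2, a reader might conclude that it will not be measured. That goes too far. Cortisol shows that a hypothesised marker can be missing from the Biomarkers section and yet be measured, and Additional file 1 (Table S1), which holds the detailed schedule of measures, is not shown. What remains is that the two sections disagree. Nor can it be said that the count of 32 outcomes is wrong, because the outcomes are not listed.

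**Conclusion.** The point holds and is minor. On the text alone, the ghrelin hypothesis is restricted by a status that arises after randomisation and that treatment may affect; testing it as written would not be a randomised comparison and would depart from intention-to-treat. Also on the text alone, IL-2 is hypothesised and absent from the blood-marker list.

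The size of the ghrelin subgroup is an inference. It rests on assumed heights of 1.50 to 1.70 m and assumed rates of 1 to 10 %, which give 0.6 to 6 of 60 women. Across that range there are too few for a useful comparison by arm, above all at 0.0015.

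Both matters concern secondary hypotheses. The primary outcomes, the sample size and the randomisation are not affected.

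**What to change.** 1. **Ghrelin.** Drop the 20 % condition from the hypothesis and state it as a comparison of rTMS with sham in all randomised participants. Treat any relation between ghrelin and weight change as exploratory, across everyone and without a cut-off. This is a change of wording; ghrelin is already measured.
2. **IL-2.** Reconcile the Hypothesis and Biomarkers sections, and Table S1 with them: either add IL-2 to the list of blood markers or delete it from the hypothesis. Deleting it costs nothing. Adding it costs one further assay; the article does not say whether samples are stored, so feasibility must be checked first.
3. **Multiplicity.** Confirm that the 32 outcomes behind the Bonferroni level match the list after this change, and recompute the level if the count moves.
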